COMBINED ASPIRIN, CLOPIDROGREL AND DIPYRIDAMOLE VERSUS ASPIRIN ALONE IN STROKE SECONDARY PREVENTION; A SAFETY TOLERABILITY AND FEASIBILTY STUDY

BACKGROUND

Stroke is a leading cause of long term disability and death around the world. Increased platelet activity plays a critical role in the physiology of stroke. The key medical strategy for the secondary prevention of stroke is anti-platelet therapy. Several antiplatelet agents have been used which inhibit different pathways of platelet activation. The earliest agent aspirin, a cyclo-oxygenase inhibitor, showed a reduction of relative risk for stroke recurrence of approximately 25% compared with placebo1. The newly developed ADP receptor blocker clopidrogrel, showed a slight benefit over aspirin2. Dipyridamole, a phosphodiesterase inhibitor and modulator of adenosine uptake, is an effective preventative agent when used alone after stroke3. Furthermore the combination of aspirin and dipyridamole was superior to either agent alone3. The European Atrial Fibrillation Trial4 found that warfarin was superior to aspirin in the secondary prevention of stroke in patients with cardioembolic cerebral ischaemia due to atrial fibrillation. However, clinical practice reveals that between 50-66% of stroke survivors are unable to take warfarin, mostly for reasons of contraindication or problems with regular monitoring of anticoagulation. We hypothesise that combination therapy with three antiplatelet agents that act through different mechanisms may maximise the benefit of antiplatelet treatment in the secondary prevention of stroke, both in patients with sinus rhythm and those with stroke who cannot be anticoagulated. In a laboratory study we found that triple antiplatelet therapy was superior to double or monotherapy in respect of inhibiting invitro platelet function, leukocyte function and the formation of platelet leukocyte conjugates5 . Provisional data from an ongoing pilot study in normal subjects and patients with previous ischaemic stroke (ethics no. EC00/08) support the concept that triple therapy is most effective in inhibiting platelet and leukocyte function ex vivo (unpublished data).

AIM

To assess the safety, tolerability and feasibility of administering triple antiplatelet therapy (aspirin, dipyridamole, and clopidrogrel) in comparison with aspirin. This study is the prelude to a large phase 3 trial to be submitted to the MRC for funding.

DESIGN

Prospective, pilot, randomised, parallel group trial.

INTERVENTIONS

Combined aspirin (75mg od, A) dipyridamole MR (200mg bd, B) and clopidrogrel (75mg od, C) versus aspirin (75mg once daily, A) alone.

ELIGIBILTY

Inclusion criteria for patients

Age 18+

Ischaemic stroke on CT/MRI within 5 years

Previous TIA within 5 years

Written informed consent from patient or assent from a legally acceptable representative

In sinus rhythm or in atrial fibrillation but not suitable for anticoagulation

Exclusion criteria

Thrombocytopenia (platelet count<100) and or anaemia (Hb<10)

Severe hypertension SBP >180 or DBP>110 mmHg

Previous cerebral haemorrhage

Hypersensitivity or intolerance to aspirin, dipyridamole or clopidrogrel

Any history of peptic ulcer or other gastrointestinal bleeding

Severe concomitant medical conditions including AIDS or cancer

Pregnancy or breast feeding

Patients needing or already receiving anticoagulant or NSAIDS other than aspirin therapy

Involvement in another secondary prevention drug trial

Not available for follow up eg. overseas visitor

METHOD

51 patients with a previous diagnosis of TIA or ischaemic stroke and in sinus rhythm within 5 years will be recruited into the trial. All those patients who have not previously received and tolerated dipyridamole will be given open label dipyridamole 200mg MR for a period of 2 weeks before randomisation (as per ref. EC00/08). This will be in addition to any aspirin therapy that these patients are already on. Only those patients that have completed 2 weeks without significant adverse events will continue into the trial. There will then be a 3 week washout period before participants are randomised to receive either aspirin 75mg daily or triple antiplatelet therapy. Patients with AF who are not being anticoagulated will also be enrolled in a similar manner. It is expected that the maximum follow up period for the first patient will be 15 months (maximum 2 years), ie. recruitment will take place over 12 months. Triple therapy will consist of a combination of aspirin (75mg daily), dipyridamole MR (200mg twice daily) and clopidrogrel (75mg daily). Prior to starting, all patients will have data collected relating to general demographics, risk factors, medications, smoking history, postural blood pressure measurement. In addition, a medical examination will be undertaken to find any clinical contraindications and baseline venous blood samples will be collected for the lab measures detailed below. Patients will then commence the randomised treatment regimen and be followed up after 2 weeks and then every three months (after the first 3 month follow up patients will be followed up by telephone every third month, the final follow up will be by a clinic visit). Blood tests will be repeated at 2 weeks and three months. Postural BP and pulse rate will be measured at 2 weeks, 3 months and final follow up. Screening for adverse events will occur at every follow up point. The study will continue until the last recruited patient has had their first 3 months follow up.

OUTCOME MEASURES

Primary

Number of subjects completing randomised treatment to final follow up.

Secondary

Recurrent ischaemic stroke

Recurrent TIA

Intracerebral haemorrhage

Major extracranial bleeding (clinically overt bleeding associated with one or more of; Transfusion of at least 2 units of red cells, a fall in Hb of at least 2g/l or bleeding leading to cessation of treatment.)

Minor extracranial bleeding (epistaxis, purpura)

Sitting and standing blood pressure, heart rate at 2 weeks, 3 months and follow up.

Presence of headache

Lab Measures

Platelet Activity and leukocyte function (as in protocol approval EC00/08)

-Full blood count (Baseline, 3, 12 and 24 months)

-Platelet count

-Platelet aggregation in whole blood by single platelet counting. (hirudin as anticoagulation, ADP, PAF , collagen and AA as agonists).

-Mean platelet volume (in whole blood)

-Activated marker on platelet. (P-selectin CD62p by flow cytometry from whole blood).

-White cell platelet aggregates (CD14 on monocytes, CD11b on neutrophils and monocytes, CD42a on platelets by flow cytometry.)

SAMPLE SIZE

Assuming an overall significance (alpha) of 0.05, power (1-beta) = 0.80, 2:1 randomisation (ACD:A), and number of subjects completing treatment to end of trial is 60% in ACD group and 89% in A group3 , the required size would be 51 patients, with 17 in the aspirin group and 34 in the ACD group. Additional patients with atrial fibrillation will be enrolled during the duration of the trial up to a maximum of 30 (ACD:20, A10).

RANDOMISATION

By stratification (sinus rhythm versus atrial fibrillation) and minimisation (age, gender, time from stroke, systolic blood pressure)

REFERENCES

1 Collaborative overview of randomised trials of antiplatelet therapy, prevention of death, myocardial infarction and stroke by prolonged anti platelet therapy in various categories of patients. BMJ 1994; 308: 81-106

2 CAPRIE Steering Committee: A Randomised, blinded, trial of clopidrogrel verses aspirin in patients at risk of ischaemic events (CAPRIE). Lancet 1996; 348:1329-1339.

3 Diener HC, Cunha L Forbes C, Sivenius J Smets P, Lowenthal A: European Stroke Prevention Study 2. Dipyridamole and acetylsalicylic acid in the secondary prevention of stroke. J Neurol Sci 1996; 143: 1-13

4 EAFT (European Atrial Fibrillation Trial) Study Group. Secondary prevention in non-rheumatic atrial fibrillation after transient ischaemic attack or minor stroke. Lancet 1993;342:1255-1262.

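### Every randomised patient is selected for dipyridamole tolerance and no outcome covers the run-in or washout, so completion and headache on triple therapy will probably look better than in unselected stroke or TIA patients.

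*Protocol*

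**What the plan says.** The AIM section sets the purpose: "To assess the safety, tolerability and feasibility of administering triple antiplatelet therapy", compared with aspirin, as a prelude to a large phase 3 trial.

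The METHOD section describes two routes to randomisation. Patients who have already received and tolerated dipyridamole skip the run-in. All others take it open label for 2 weeks, on top of any aspirin they already use, and then: "Only those patients that have completed 2 weeks without significant adverse events will continue into the trial". A 3-week washout comes before randomisation. Patients with atrial fibrillation are enrolled in a similar manner. Follow-up visits start 2 weeks after randomised treatment begins, and adverse events are screened at those visits.

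Under OUTCOME MEASURES, the primary outcome is the number of subjects who complete randomised treatment to the final follow-up. Secondary outcomes include bleeding, recurrent stroke and TIA, and "Presence of headache".

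The SAMPLE SIZE section assumes that the "number of subjects completing treatment to end of trial is 60% in ACD group and 89% in A group", with a reference mark after the aspirin figure. It arrives at 51 patients, 17 on aspirin and 34 on triple therapy.

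**The concern.** Dipyridamole is one of the three drugs in the triple arm and is absent from the aspirin arm. A patient who cannot take it during the first 2 weeks is a tolerability failure of the regimen under study. Under the protocol that patient leaves before randomisation and is counted nowhere: not in completion, not in headache, not in the safety outcomes. Events in the washout are likewise outside the follow-up schedule.

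Two things are at stake. First, the completion figure handed to phase 3 planning describes proven tolerators, whereas the BACKGROUND hypothesis concerns stroke patients generally. Second, if the 60% was meant for patients who had not passed a run-in, the contrast between the arms will be smaller than the 29 points planned for. The trial would then be less able to show that triple therapy is harder to complete.

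**Working it through.** **Who is counted.** Setting the sections side by side:

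- Entry: by previous tolerance, or by passing the run-in (METHOD). Known intolerance of any study drug is also an exclusion (ELIGIBILITY). There is no third route, so all randomised patients are dipyridamole-tolerant by selection.
- Primary outcome: completion of randomised treatment. A run-in failure is never randomised and cannot be counted.
- Adverse-event screening: at follow-up points, which all fall after randomised treatment starts.

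So neither the run-in nor the washout contributes to any stated outcome.

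**Reproducing the sample size.** Inputs from the SAMPLE SIZE section: alpha 0.05 (sidedness not stated), power 0.80, ratio 2:1, completion 0.89 on aspirin and 0.60 on triple therapy. With unpooled variance, the aspirin group size is

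n = [0.89 × 0.11 + (0.60 × 0.40)/2] × (z_alpha + z_beta)² / 0.29²

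One-sided: (0.0979 + 0.12) × (1.645 + 0.842)² / 0.0841 = 16.02, rounded up to 17. Then 17 + 34 = 51, as stated. Two-sided, the same formula gives 20.34, rounded up to 21, a total of 63. Pooled-variance versions give 63 (one-sided) and 81 (two-sided). The one-sided unpooled formula is therefore used below, because it matches the plan.

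**If 60% is not a post-run-in figure.** Let f be the share of otherwise eligible patients removed by the run-in. The protocol does not give f; 5% to 20% is an assumed range. As an upper bound, suppose that every patient removed would have stopped triple therapy and that aspirin completion stays at 89%. Then

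p = 0.60 / (1 − f)

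power = Φ[(0.89 − p) / √(0.0979/17 + p(1 − p)/34) − 1.645]

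At f = 0: 0.29 / √(0.00576 + 0.00706) = 0.29 / 0.1132 = 2.56; 2.56 − 1.645 = 0.92; power 0.82.

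| f | p on triple therapy | difference (points) | power at 17:34 | total N for 80% power |
|---|---|---|---|---|
| 0 | 60.0% | 29.0 | 82% | 51 |
| 5% | 63.2% | 25.8 | 74% | 60 |
| 10% | 66.7% | 22.3 | 64% | 78 |
| 20% | 75.0% | 14.0 | 37% | 183 |

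**How far this is an upper bound.** If those removed would have completed triple therapy at rate c, then p = (0.60 − f × c)/(1 − f). With f = 10% and c = 30%, p = 0.57/0.90 = 63.3% and power is about 74% rather than 64%. With c = 60% there is no shift.

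**If 60% is already a post-run-in figure,** the f = 0 row applies and power is unchanged.

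**The case against.** The selection is openly stated and extends an existing exclusion for known intolerance. Randomisation follows it, so the comparison is sound for the patients randomised. The run-in tests neither clopidogrel nor the triple combination, so bleeding on triple therapy and later stopping remain fully observed. If phase 3 used the same run-in, the completion rate would carry over to its randomised patients. Staff must judge run-in adverse events to apply the continuation rule, and the run-in follows another approved protocol that is not shown, so some recording may already exist. All of this stands. It limits the point without removing it, because the protocol places none of that information in an outcome.

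Three stronger readings are tempting, and the document does not support them.

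- A reader might infer that the run-in invalidates the 60% assumption. The protocol does not say whether 60% applies before or after the run-in. It attaches the figure to a randomised group, which exists only after the run-in, so a post-run-in meaning is at least as natural.
- A reader might infer that the run-in brings power down to 58% or less. A pooled two-sided calculation gives 58% at f = 0 and 19% at f = 20%. But the gap between the planned 80% and 58% comes from the choice of test, a separate matter, and is there with no run-in effect at all.
- A reader might infer that only the triple arm benefits. The continuation rule is not limited to dipyridamole-related events, and the run-in is taken with any existing aspirin. It may also remove patients who would have stopped aspirin. The net effect probably favours triple therapy, but its size is unknown.

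**Conclusion.** The point holds as a limit on what the trial can conclude and as a gap in what it counts. Completion and headache on triple therapy will be observed in dipyridamole-tolerant patients only and will probably look better than in unselected stroke or TIA patients. The randomised comparison is not biased for the population it enrols; overstatement arises only when the result is carried to patients who have not been selected.

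The effect on power depends on the 60%. If it is a post-run-in figure there is none. If it is not, power falls from 82% to at worst 74%, 64% and 37% for 5%, 10% and 20% removed. This rests on the assumed range of f, on all those removed being future non-completers, on unchanged aspirin completion, and on the one-sided unpooled formula.

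**What to change.** Keep the run-in and count it.

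1. Log every patient who enters the run-in, every failure with its reason, and every bleed, stroke, TIA, headache and death from the start of the run-in to the end of washout.
2. Report the run-in failure proportion as a tolerability and feasibility outcome beside the randomised result.
3. Give overall completion (run-in pass rate times completion on triple therapy) only among patients who entered the run-in. Report previous tolerators separately: their earlier selection is unobserved, so a product that includes them would describe neither group. For illustration, a 90% pass rate and 66.7% completion among those who passed would give 0.90 × 0.667 = 60% of entrants.
4. Limit the conclusion on completion to dipyridamole-tolerant patients.
5. In SAMPLE SIZE, state whether the 60% is a post-run-in figure and what it is based on. If it is not, revise it and the power with it.

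The cost is a run-in log, one extra table and a less favourable feasibility figure. Items 1 to 4 need no extra patients or visits; item 5 could raise the sample size only if the 60% proves not to be post-run-in.

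### The primary outcome, completion to final follow-up, has no time horizon, and neither do the 60% and 89% rates behind the sample size

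*Protocol*

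**What the plan says.** Under Outcome Measures, the primary outcome is "Number of subjects completing randomised treatment to final follow up". No month is attached to it. Three statements under Method determine when final follow-up falls:

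- "recruitment will take place over 12 months".
- "The study will continue until the last recruited patient has had their first 3 months follow up".
- "It is expected that the maximum follow up period for the first patient will be 15 months (maximum 2 years").

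The last contact is in person ("the final follow up will be by a clinic visit"), again without a month. The Lab Measures list includes a blood count at 24 months.

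Under Sample Size, the planning assumption is "number of subjects completing treatment to end of trial is 60% in ACD group and 89% in A group3". With "Assuming an overall significance (alpha) of 0.05", "power (1-beta) = 0.80" and 2:1 allocation, the protocol arrives at 51 patients: 34 on triple therapy (ACD) and 17 on aspirin (A). It does not state whether the test is one- or two-sided, or over what period the two rates apply.

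**The concern.** Final follow-up is a common calendar close, not a fixed time after randomisation. On the expected timetable the earliest patient must stay on treatment about five times as long as the latest to be counted the same way. A slow or front-loaded recruitment would change the completion proportion even if tolerability were identical.

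The Aim describes the trial as a safety, tolerability and feasibility study leading to a large phase 3 trial. Persistence on triple therapy is the figure that trial needs. A proportion averaged over an unplanned mix of exposure times is not a 3-month, 12-month or any other rate, so it cannot be used directly to plan a trial of fixed duration.

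The sample size has the same gap. Whether the assumed 29-point difference would be seen depends on how the period behind 60% and 89% compares with the exposure patients actually get.

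**Working it through.** **1. The plan's own figure.** Inputs from Sample Size: pA = 0.89, pACD = 0.60, 2:1 allocation, alpha 0.05, power 0.80. The two-proportion formula with unpooled variance and one-sided alpha gives

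nA = (0.89×0.11 + 0.60×0.40/2) × (1.645 + 0.842)² / 0.29² = 16.02, rounded up to 17.

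This gives 17 + 34 = 51, as stated. The other common variants do not: pooled one-sided gives 63, pooled two-sided 81, and unpooled two-sided about 61 before rounding to whole 2:1 groups.

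Power at 17 and 34 under the matching formula: SE = √(0.89×0.11/17 + 0.60×0.40/34) = 0.1132; 0.29/0.1132 − 1.645 = 0.917; power 82%. A two-sided pooled test with the same inputs has 58% power. These two values are the baselines for what follows.

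**2. Spread of follow-up.** Twelve months of recruitment plus a 3-month minimum gives 3 to 15 months. If entry is uniform (an assumption), the mean is (3 + 15)/2 = 9 months.

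**3. Expected completion.** Let H be the month to which 60% and 89% refer. The protocol does not give it, so a range is shown. With a constant discontinuation hazard (an assumption), λ = −ln(p)/H, and

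expected completion = (e^(−3λ) − e^(−15λ)) / (12λ).

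For H = 12:

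- ACD: 12λ = 0.5108, so (0.8801 − 0.5281)/0.5108 = 0.689.
- A: 12λ = 0.11653, so (0.97129 − 0.86445)/0.11653 = 0.917.
- The gap is 0.228 and its SE 0.1039; 0.228/0.1039 − 1.645 ≈ 0.547, so power is 71%.

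| Month behind 60%/89% | ACD | A | Gap (points) | Power, one-sided unpooled | Power, two-sided pooled |
|---|---|---|---|---|---|
| As planned | 60% | 89% | 29 | 82% | 58% |
| 9 | 61% | 89% | 28 | 80% | 55% |
| 12 | 69% | 92% | 23 | 71% | 43% |
| 15 | 74% | 93% | 19 | 63% | 34% |
| 24 | 83% | 96% | 13 | 48% | 21% |

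If the rates described a period shorter than about 9 months, the gap and the power would be larger than planned. For example, 3-month rates give 26% v 71% and 96% power by the one-sided formula.

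**4. What is being pooled.** If the rates are 15-month rates, a patient followed for 3 months completes with probability 0.60^(3/15) = 90% on ACD and 0.89^(3/15) = 98% on A. One followed for 15 months completes with probability 60% and 89%. Both patients carry equal weight in the count.

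**5. Sensitivity.**

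- *Early stopping.* Replace t/H by (t/H)^0.5 in the exponent. Twelve-month rates then give 65% v 91% (one-sided power 76%), and 24-month rates give 74% v 93% (64%).
- *Longer follow-up.* With follow-up uniform over 3 to 24 months and constant hazard, 12-month rates give 58% v 88% and 82% power, so the loss disappears. With 24-month rates it is 76% v 94% and 61%.

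**The case against.** Several points on the other side stand.

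- **No bias between arms.** Patients are randomised concurrently, so follow-up should be distributed alike in both arms. A reader might infer a distorted treatment comparison; nothing in the protocol supports that.
- **Power does not fall from 80% to 43%, 34% or 21%.** Setting the two-sided pooled figures against the stated 80% mixes two issues. That test has only 58% at exactly 60% v 89%, with no horizon problem at all. The part due to the horizon is 82% to 71%, 63% or 48% by the formula that reproduces 51, or 58% to 43%, 34% or 21% by the other.
- **The 15 months and the 2 years are not a contradiction.** The sentence reads naturally as an expected value with an upper cap. The cap does widen the possible range beyond 15 months.
- **The wording of the endpoint and of the planning rates agrees.** Both refer to the close of the trial. A reader might go further and say the rates come from a cited trial of a different length. The reference mark stands after the aspirin rate only, and the duration of that study is not in the document, so a mismatch cannot be shown. What can be shown is that no duration is given.
- **The magnitudes are model-based.** Constant hazard and uniform entry are not in the protocol, and the sensitivity results show smaller losses under other assumptions.

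It can also be said that log-rank tests and Kaplan-Meier curves belong in a statistical analysis plan, and that persistence curves could be drawn from the planned contacts anyway. That does not settle the point. The definition of the primary outcome is fixed in the protocol, and followed as written it yields a proportion with no time attached.

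**Conclusion.** The point holds as one of definition and interpretation. The primary outcome requires between about 3 and an expected 15 months on treatment (cap 2 years), depending on the date of entry. The resulting proportion reflects recruitment speed as well as tolerability and does not transfer to a phase 3 trial of fixed duration.

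The consequence for power is conditional. Under uniform entry over 12 months and constant hazards, the planned gap is roughly kept if 60% and 89% describe about 9 months. Later reference months reduce it, earlier ones increase it, and the document does not let a reader tell which applies. The stronger claim that the trial is certainly underpowered for this reason is not supported. This should be corrected, but it does not invalidate the comparison.

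**What to change.** Define the primary outcome as time from randomisation to permanent discontinuation of randomised treatment, censored at study close. Compare the arms by a log-rank test stratified by rhythm, which is already the randomisation stratum. Report Kaplan-Meier persistence by arm with 95% confidence intervals at stated months: 3 months, which every patient can reach, and 12 months. Note beside the 12-month figure that, with uniform entry over 12 months, only (15 − 12)/12 = one quarter of patients, about 13 of 51, can be followed that long, so it will be imprecise. Under Sample Size, state the month to which 60% and 89% refer and restate the power for it.

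A binary outcome at 3 months is a tempting shortcut and is not recommended. With 12-month rates and constant hazard it would compare 0.60^(3/12) = 88% with 0.89^(3/12) = 97%, a gap of 9 points, with about 14% two-sided pooled power at 34:17.

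The cost is small. A stop date must be recorded, which the contacts at 2 weeks and then every three months allow, and the restated power may be less favourable. Power itself is about unchanged: in simulation at 34:17 with 12-month rates, the log-rank test had 43% and the binary chi-square test 44%. The gain is in interpretability.

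### The listed bleeding outcomes leave no place for subdural, extradural or subarachnoid haemorrhage, so the bleeding comparison could be incomplete

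*Protocol*

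**What the plan says.** The Aim section of the protocol puts safety first: "To assess the safety, tolerability and feasibility of administering triple antiplatelet therapy", with aspirin as the comparator.

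Under Outcome Measures, the primary outcome is "Number of subjects completing randomised treatment to final follow up". The secondary list opens with "Recurrent ischaemic stroke" and recurrent TIA, and then gives three bleeding outcomes:

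- "Intracerebral haemorrhage", with no definition.
- Major bleeding, worded as "Major extracranial bleeding (clinically overt bleeding associated with one or more of" three criteria: transfusion, a fall in haemoglobin, or stopping treatment because of the bleed.
- Minor bleeding, also limited to extracranial sites, with nosebleeds and purpura as the examples.

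Blood pressure, heart rate and headache complete the clinical outcomes, and laboratory measures follow. The list has no line for all intracranial haemorrhage, haemorrhagic stroke, stroke of any type, or major bleeding at any site.

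The Method section adds: "Screening for adverse events will occur at every follow up point". It gives no classification of bleeding events for that screening.

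**The concern.** The bleeding outcomes are divided by site, and the division is not complete. One outcome covers bleeding into the brain substance and two cover bleeding outside the skull. Bleeding inside the skull but outside the brain substance falls between them. The severity criteria do not help, because they are attached to the extracranial outcome only: a subdural bleed that led to treatment being stopped would satisfy the cessation criterion and still be excluded by its site. As worded, a nosebleed is a named bleeding outcome and a fatal subdural bleed is not.

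Bleeding is the obvious safety question when three antiplatelet agents are compared with one, and the Aim section describes the study as the step before a large phase 3 trial. At stake is whether the bleeding count passed on to that trial includes every serious bleed. The protocol itself fixes the outcome list, so this is not a detail that it leaves to an analysis plan.

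**Working it through.** **Step 1: match each type of bleed to the listed outcomes.** The inputs are the outcome lines under Outcome Measures, read literally.

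| Event | Intracerebral line | Major or minor extracranial lines | Ischaemic stroke / TIA lines |
|---|---|---|---|
| Bleed into brain substance | yes | no | no |
| Subdural | no (outside brain substance) | no (inside skull) | no |
| Extradural | no (outside brain substance) | no (inside skull) | no |
| Subarachnoid | no (outside brain substance) | no (inside skull) | no (not ischaemic) |
| Gastrointestinal bleed, nosebleed | no | yes | no |

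Three types of intracranial bleed meet no bleeding or stroke outcome.

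**Step 2: where else would such a bleed be recorded?**

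- *Adverse-event screening* would pick it up, but without placing it in a bleeding category.
- *The headache outcome* might register a symptom of it, not the bleed.
- *The primary outcome* would count the patient as a non-completer if the bleed ended treatment or was fatal before final follow-up, but would not say why. The Sample Size section assumes 60% completion on triple therapy, hence 1 − 0.60 = 40% non-completion. In 34 patients that is 0.40 × 34 = 13.6 expected non-completers. One intracranial bleed would be one unlabelled case among about 14.

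**Step 3: size of one uncounted event.** The protocol gives no rate for these bleeds, so an expected number cannot be calculated. What can be shown is the weight of a single event. The group sizes are those in the Sample Size section: 34 triple therapy and 17 aspirin, plus up to 20 and 10 more with atrial fibrillation. The outcome list is not restricted to sinus rhythm, so both denominators are relevant.

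| Group | Sinus rhythm only | With full atrial fibrillation enrolment |
|---|---|---|
| Triple therapy | 1/34 = 2.9% | 1/(34 + 20) = 1/54 = 1.9% |
| Aspirin | 1/17 = 5.9% | 1/(17 + 10) = 1/27 = 3.7% |

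The bleeding proportion in the arm concerned would be too low by that amount for each such event. The protocol states no figure for bleeding that could be reproduced, and the argument does not depend on how the total of 51 was derived.

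**The case against.** **Such a bleed would not be lost.** Adverse events are screened at every follow-up, nothing says that they will not be tabulated by arm, and an analysis plan may do so. This stands as a limit on severity. It does not close the gap: an event recorded among general adverse events is not counted in a prespecified bleeding outcome.

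**The authors may have used the term loosely.** Pairing it with extracranial bleeding could suggest a split between inside and outside the skull. The protocol gives no definition to support that reading. If it was meant, the wording still has to say so.

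**Deaths.** All-cause death is not a listed outcome, and a reader might infer that a fatal event outside the listed types is never compared between arms. The protocol does not support that. A patient who dies before final follow-up has not completed treatment and enters the primary between-arm comparison as a non-completer. What is missing is a separate label.

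**Direction of bias.** A reader might also infer that the result would be tilted towards triple therapy looking safe. That would require these bleeds to occur, to be more frequent on triple therapy, and to be ignored in the safety report. The protocol establishes none of these. The understatement applies to whichever arm has the event.

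**Confidence limits as a measure of size.** The exact two-sided 95% upper limits are 10.3% for 0/34 and 15.3% for 1/34 (6.6% and 9.9% for 0/54 and 1/54). They would be the same for any rare event under any definition. They describe the imprecision of a small pilot, not the effect of this wording.

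**Conclusion.** The point holds in a limited form. Read as written, the outcome list counts a subdural, extradural or subarachnoid bleed in no bleeding outcome, so the bleeding comparison in a study with a safety aim could be incomplete. Each such event would leave the bleeding proportion too low by 1.9 to 2.9 percentage points if it occurred on triple therapy, or by 3.7 to 5.9 points if on aspirin, depending on how many atrial fibrillation patients are enrolled.

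This assumes that the term is taken in its literal sense (bleeding into brain substance) and that the planned group sizes are reached. It does not assume that such bleeds are likely, or commoner in one arm. The sample size and the primary outcome are unaffected. It is a wording fault in a secondary outcome, worth correcting because the trial is small and bleeding is its main safety question.

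**What to change.** In the secondary outcome list, replace the intracerebral line with: *any intracranial haemorrhage (intracerebral, subdural, extradural, subarachnoid), with intracerebral shown separately*. Together with the existing extracranial lines, this gives every bleed a place by site.

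Make the change before outcomes are compared by arm, so that no bleed has to be assigned to a category after it has been seen.

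Listing all-cause death as its own secondary outcome is optional. It would make deaths visible by name, but they already count in the primary outcome when they occur before final follow-up.

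The cost is an amendment to wording. The events are already sought by the adverse-event screening, so no extra visits, tests or patients are needed.
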